## Abstract

**Background:**

Opioid dependence is an increasing public health problem all over the world. Patients with opioid dependence have to receive methadone maintenance therapy (MMT) as replacement therapy for years or even for their entire life. Acupuncture as a kind of therapy has been used to treat substance dependence for many years. Jin’s three-needle acupuncture (JTN), a type of acupuncture technique, has been applied to treat various diseases for several decades. However, JTN as an acupuncture technique has not been used to treat patients receiving MMT. Therefore, we designed a randomized controlled trial to evaluate the efficacy and safety of acupuncture as adjunctive therapy for patients receiving MMT.

**Methods/design:**

This study is a parallel-arm, randomized controlled trial that aims to evaluate the efficacy and safety of acupuncture as adjunctive therapy for patients receiving MMT. A total of 140 eligible participants who range in age from 18 to 60 years and fulfil the Diagnostic and Statistical Manual of Mental Disorders, 5th edition (DSM-V), for opiate dependence will be enrolled into this study. All eligible participants will be randomly assigned to the acupuncture group or routine group in a 1:1 allocation ratio. Participants who are enrolled in the acupuncture group will receive MMT and JTN treatment for 30 min per session. Meanwhile, those who are assigned to the routine arm will receive MMT only. All 18 sessions of JTN treatment will be delivered over 6 weeks (3 per week) and followed by a 4-week follow-up period. The primary outcome measure will be the visual analogue scale (VAS) for drug craving and the daily consumption of methadone (DCOM). Secondary outcome measures will include the urine test for opioid use, the 36-item Short Form Survey (SF-36), the Beck Anxiety Inventory (BAI), the Beck Depression Inventory II (BDI-II) and Pittsburgh sleep quality index (PSQI). VAS, DCOM, BAI, BDI-II and the urine test for opioid use will be evaluated at baseline, the second week, the fourth week, the sixth week and the tenth week. SF-36 and PSQI will be assessed at baseline, the fourth week, the sixth week and the tenth week.

**Discussion:**

The results of this trial will provide evidence on the efficacy and safety of acupuncture as adjunctive therapy for patients receiving MMT.

**Trial registration:**

Chinese Clinical Trial Registry ChiCTR1900026357. Registered on 2 October 2019.

## Background

According to the World Drug Report 2018, approximately 31 million people are affected by opioid use disorders through the world, which cause the greatest burden of severe disease and drug-related deaths worldwide [1]. In China, there are approximately 2.5 million people using illicit drugs, of which opioids and methamphetamines represent the majority [2].

Opioid dependence is a chronic psychiatric disorder. Discontinuation of the drug abruptly induces specific physiological and psychological changes called withdrawal, which is a temporary stage opposing intoxication towards re-establishment of the patient’s neuronal system. Withdrawal symptoms mainly include sweating, shaking and diarrhoea in the first few days, accompanied by dysphoria, depression, anxiety and insomnia, which may continue for several months [3, 4]. It is an unadaptable state associated with withdrawal symptoms and severe craving, which may lead to the high risk of relapse. The primary goal of treatment for opioid dependence usually focuses on achieving control of withdrawal symptoms and reducing cravings. Methadone has been used to treat withdrawal symptoms for several decades. Patients with opioid dependence have to receive MMT as replacement therapy for years or even their entire life. However, side effects of MMT still exist and have been reported to range widely, especially during the early weeks of methadone stabilization [5]. Patients often complain of insomnia and cravings during MMT, which contribute to the risk of relapse [6]. Therefore, it is necessary to seek a new treatment with efficacy and safety for patients receiving MMT.

Acupuncture has been applied to treat diseases in China for thousands of years, gaining popularity in Western countries as an alternative and complementary therapy [7]. In 1996, the World Health Organization accepted that acupuncture, as a kind of therapy, is appropriate for the treatment of drug use disorders [8]. Compared with drug treatment, acupuncture for opioid dependence has zero side effects and is convenient and inexpensive [9]. Acupuncture may inhibit the activation of specific brain regions related to drug craving, which support its potential as a therapy for drug craving [10]. Liang Yan reported that acupuncture may alleviate the depression and anxiety associated with heroin dependence [11]. Some basic studies have revealed that acupuncture might potentially reduce relapse through inhibiting attention bias to heroin [12], lowering complications of drug dependence [13] and modifying the morphine withdrawal syndrome [14]. To our knowledge, JTN, a type of acupuncture technique, has been applied to treat diseases for decades and has formed a school of acupuncture technique in South China. The concept of ‘mind’ means mental activities in traditional Chinese medicine (TCM). JTN is able to treat mental diseases and help patients to regulate the mind [15]. JTN has been widely used to ameliorate depression and anxiety [16]. A previous study reported that JTN treatment may ameliorate insomnia [17]. We hypothesize that patients receiving JTN will have reductions in drug craving, require less methadone during MMT and have improvements in quality of life, sleep quality, depression and anxiety. Therefore, this study aims to evaluate the efficacy and safety of acupuncture as an adjunctive therapy for patients receiving MMT.

## Methods

### Study design

This is a parallel-arm, randomized controlled trial to evaluate the efficacy and safety of acupuncture as an adjunctive therapy for patients receiving MMT. All eligible individuals (140) will be randomly assigned to the acupuncture group (*n* = 70) or the routine group (*n* = 70) in a 1:1 ratio. This study protocol has been approved by the Ethics Committee of the First Affiliated Hospital of Guangzhou University of Chinese Medicine (No.Y-2019-241) and registered in the Chinese Clinical Trial Registry (ChiCTR1900026357). This study protocol conforms to the Standard Protocol Items: Recommendations for Interventional Trials (SPIRIT) guidelines (Additional file 1) [18] and the Standards for Reporting Interventions in Controlled Trials of Acupuncture (STRICTA) checklist (Additional file 2) [19]. Before randomization, all eligible participants will be asked to sign an informed consent. The flowchart of the study is shown in Fig. 1.

**Fig. 1 Fig1:**
[figure not shown]
Flowchart of trial procedures

### Study subjects

Subjects will be recruited through advertisements at the Affiliated Brain Hospital of Guangzhou Medical University. All eligible individuals will be strictly assessed by an acupuncturist based on the criteria described below. Subjects are eligible to include if they (1) are male or female aged 18–60 years; (2) fulfil the criteria for the diagnosis of opioid dependence on the basis of the Diagnostic and Statistical Manual of Mental Disorders, 5th edition (DSM-V) [20]; (3) receive MMT for more than 30 days; (4) do not receive any kind of acupuncture therapy during the previous 3 months; and (5) are able to sign informed consent.

Subjects will be excluded if they have one or more of the following criteria: (1) serious heart, liver, lung or kidney disease; (2) venereal disease or AIDS; (3) the presence of severe digestive disease and athrepsia; (4) major psychosis; (5) the receipt other treatment that may affect the efficacy evaluation of the present intervention; (6) an infection, inflammation, scar or injury close to the site of the selected acupoints; or (7) are pregnant or planning to become pregnant.

### Randomization, allocation and concealment

Eligible patients will be randomly assigned in an equal ratio to the acupuncture group or the routine group via a central randomization system. The randomization sequence will be generated in a block size of 4. Participants will be informed that they have an equal chance to be assigned to the acupuncture group or the routine group. After participants sign the informed consent form and complete baseline assessments, the researcher will assign them a randomization number and allocate the participants to each group. The allocation of participants will be performed by an independent researcher at the clinical site who was not involved in the assessment of outcomes. Due to the design of this study, practitioners and eligible subjects will know the allocated group, while the outcome assessors, data collectors and statisticians will be blinded to group allocations during the study.

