### Sample size calculation

The primary outcome measure for drug craving is VAS. Based on previous studies [5, 30], after 4 weeks of treatment, the VAS for drug craving score difference between the baseline and the endpoint in the sham acupuncture group should be approximately 20 ± 30, while the true acupuncture group should be approximately 37.5 ± 28. Type 1 error is assumed at 0.05, and type 2 error is assumed at 0.1. PASS11.0 software (CSS Statistical Software, Kaysville, UT, USA) has been used to determine the sample size, and the minimum sample size is 60 subjects for each group. Considering a dropout rate of 15%, a total of 140 subjects will be required with 1:1 allocation to each group (70 participants per group) for this study.

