## Discussion

To our knowledge, JTN treatment for patients receiving MMT has not been intensively investigated. This study describes the protocol of a randomized controlled trial to test the effectiveness and safety of acupuncture as an adjunctive therapy for patients receiving MMT.

JTN, a type of acupuncture technique, has been practised for decades. One of the features of JTN is choosing treatment acupoints in a unique way. The prescription of JTN is comprised of several acupoint groups, and each acupoint group consists of three or four special acupoints that are based on local points, influential points or empirical points. The law of combination of these points may have more effectiveness to treat disease than a normal mixture of ‘cookbook’ points.

According to previous studies, the effectiveness of acupuncture as an adjunct therapy in patients receiving MMT has been controversial. Bearn reported a lack of effect for adjunctive MMT with auricular acupuncture upon withdrawal symptoms or drug craving [31]. Pei Lin showed a lack of effect for adjunctive MMT with auricular acupuncture upon the number of daily consumed cigarettes, withdrawal syndrome and relapse rate [32]. However, several studies have reported positive findings in the effectiveness of acupuncture for the treatment of drug dependence [33–35]. Chan claimed that 4 weeks of acupuncture as an adjunct to MMT may reduce the daily dosage of methadone and may cause a greater improvement in sleep latency [5]. Although JTN has been practised for several decades, this is the first time that JTN will be applied to treat opioid dependence. According to the theory of TCM, the acupoints we choose may help to tranquilize and free the body from tension, which may have the potential to ameliorate several mental or physical symptoms of opioid dependence.

One important limitation of our study is that it is an open-label trial, making it impossible to execute a blinding method. Patients may have strong treatment preferences for acupuncture, which may produce adjuvant treatment effects. To reduce this kind of bias, the acupuncturists and outcome assessors will be different, which will maintain the objectivity of assessment of outcomes. We will exclude the investigators and statisticians from randomization as well, to make sure all of them are blind to allocation.

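### A single disclosed block size of 4 in an open-label trial lets anyone who follows past allocations foresee about one in three; whether the acupuncturist who screens patients can do so is not stated

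*Protocol article*

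**What the plan says.** All references are to the protocol article. Under Randomization, allocation and concealment it states "Eligible patients will be randomly assigned in an equal ratio to the acupuncture group or the routine group via a central randomization system", and then "The randomization sequence will be generated in a block size of 4". No varying or withheld block size is mentioned, and no stratification. The same section says "The allocation of participants will be performed by an independent researcher at the clinical site who was not involved in the assessment of outcomes", and that allocation follows consent and the baseline assessments.

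On who knows the arm, that section says "practitioners and eligible subjects will know the allocated group". The Discussion adds "One important limitation of our study is that it is an open-label trial, making it impossible to execute a blinding method". It also says that investigators and statisticians are kept out of randomisation so that they remain blind to allocation.

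On recruitment, Study subjects says "Subjects will be recruited through advertisements at the Affiliated Brain Hospital of Guangzhou Medical University" and "All eligible individuals will be strictly assessed by an acupuncturist based on the criteria described below". Trial status reports that enrolment was already under way when the article was written. Sample size calculation gives the target: "a total of 140 subjects will be required with 1:1 allocation to each group (70 participants per group) for this study".

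**The concern.** A 1:1 block of 4 always holds two patients of each arm. Once two of one arm have appeared, the rest of the block is fixed. In an open-label trial the treatment itself shows past allocations: patients who attend for needling are in the acupuncture arm, and enrolled patients who do not are in the routine arm. A person who also knows the order of enrolment and the block size can often tell what comes next.

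This matters if that person influences who enters and when. Several exclusion criteria call for judgement, such as how serious an organ disease is, what counts as major psychosis, and which concurrent treatments could disturb the efficacy evaluation. The article also concedes that patients may strongly prefer acupuncture, and one primary outcome is a craving scale marked by patients who know their arm. Steering more promising or more willing patients towards one arm, even without intent, would bias the comparison at entry. Blinding the outcome assessors does not protect against that.

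**Working it through.** **Inputs from the article.** Block size 4, ratio 1:1, 140 patients. From Sample size calculation: VAS changes of 20 (SD 30) and 37.5 (SD 28), a difference of 17.5 mm.

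**Assumptions.** No stratification, so 140 / 4 = 35 complete blocks. The observer knows the block size and every earlier allocation in order.

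**The plan's own figures.** The article gives no predictability figure. Its sample size reproduces closely: pooled SD = √((30² + 28²)/2) = 29.02, which needs 59 per group for 90% power by the t test (60 stated). With 15% dropout, 60 / 0.85 = 70.6, against 70 stated. These figures serve below only for the 140 and the 17.5 mm.

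**Places known with certainty.** The fourth place is always determined. The third is determined when the first two match, which has probability 1/3.
- Per block: 1 + 1/3 = 4/3 places of 4, or 33.3%.
- Over 35 blocks: 35 × 4/3 = 46.7, about 47 of 140.

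**Best-guess accuracy**, always guessing the arm with more places left:
- place 1: 1/2
- place 2: 2/3
- place 3: (1/3 × 1) + (2/3 × 1/2) = 2/3
- place 4: 1
- total 2.833 of 4 = 70.8%, against 50% without blocking.

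**What this could do to the VAS comparison.** Let δ be the difference in expected VAS change between patients admitted when acupuncture is guessed and when routine is guessed, and p the guess accuracy. The bias is then δ × (2p − 1). The article gives no δ, so the values are illustrative.

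| Scenario | Bias |
|---|---|
| No tracking (p = 0.5), any δ | 0 mm |
| Perfect tracking, δ = 5 mm | 5 × 0.417 = 2.1 mm |
| Perfect tracking, δ = 10 mm, acting only on certain places | 10 × 1/3 = 3.3 mm |
| Perfect tracking, δ = 10 mm, acting on every guess | 10 × 0.417 = 4.2 mm (24% of 17.5) |

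**Other block schemes**, for an observer who knows which sizes are in use. Fixed sizes are exact; mixed sizes come from simulation with 140 patients.

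| Scheme | Certain in advance | Guess accuracy |
|---|---|---|
| Fixed 4 | 33.3% | 70.8% |
| Fixed 6 | 25.0% | 68.3% |
| Fixed 8 | 20.0% | 66.6% |
| Random 4/6 | about 5.5% | 69.2% |
| Random 4/6/8 | about 2.3% | 67.9% |

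Under random 4/6/8, the δ = 10 mm bias acting on every guess falls only to 10 × (2 × 0.679 − 1) = 3.6 mm. Acting on certain places alone, it falls from 3.3 mm to about 0.2 mm.

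**The case against.** The strongest objection is that the chain from block size to bias has an undocumented link. Acupuncturists deliver the treatment and an acupuncturist judges eligibility, so a reader might infer that the screener sees the allocations. The article does not say so. Sharing a profession is not the same as having access, and the Discussion says investigators are blind to allocation. If the screener counts as an investigator, blinding is claimed; if as a practitioner, the randomisation section says the opposite. This part of the objection stands and makes the finding conditional. It does not remove it, because the text leaves the screener's position open.

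Second, allocation is central and carried out by an independent researcher. That hides the list. It does not stop anyone from inferring the next place from visible past allocations.

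Third, screening tests, consent and baseline assessment come before allocation. A screener would have to foresee which place the patient will eventually take, and overlapping screening could change the order. Unstated stratification would also make tracking harder. Both points stand: they reduce predictability without abolishing it.

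Fourth, the 4.2 mm figure requires perfect tracking and an assumed shift acting on every patient. That stands, and it is why zero is included in the range.

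Fifth, a reader might conclude that no analysis could repair such selection. That is too strong. Craving, methadone consumption, anxiety, depression, quality of life and sleep are all measured at baseline, so adjustment could remove the part acting through them. It could not remove selection on unmeasured motivation or expectancy.

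Finally, a small fixed block is a permissible choice that keeps the arms balanced, and the article does not contradict itself on block size. That is true, but the same balance is nearly as well kept by schemes that are much harder to read.

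**Conclusion.** The point holds as a conditional risk. For someone who knows the block size of 4 and all earlier allocations in order, one third of places (about 47 of 140) are certain and 70.8% can be guessed correctly. These figures are exact, given unstratified complete blocks. Disclosing the size during enrolment in an open-label trial makes the first condition easy to meet. Whether the person judging eligibility meets the second is not stated.

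The resulting bias in the VAS comparison is 0 with no tracking and at most about 4 mm with perfect tracking and an assumed 10 mm shift. The documents supply no value for that shift. A reader might take this as evidence that allocations were foreseen or patients steered; nothing in the documents shows that either happened. The change is worth making because it costs little, not because bias has been shown.

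**What to change.** For the patients still to be enrolled, have the central system generate a new sequence with randomly varying block sizes, for example 4, 6 and 8, and withhold the sizes and their order from site staff. This takes certain places from 33.3% to about 2%. It does little for probabilistic guessing (70.8% to about 68%), so it should not stand alone.

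In addition, have eligibility confirmed and locked before randomisation by a clinician who is already employed, is qualified to judge the criteria, neither treats trial patients nor has access to earlier allocations. The outcome assessors should not be given this task by default: they are blinded, but the article does not show that they are qualified to judge diagnosis, psychosis or organ disease. The protocol should also state whether the screening acupuncturist treats patients or sees allocations, and reconcile the Discussion's statement that investigators are blind with the randomisation section's statement that practitioners are not.

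The cost is a new sequence and a change in who signs eligibility, with no extra staff if a suitable clinician is already in post. Outcomes and sample size are untouched. The statistical downside is a slightly larger possible imbalance between the arms at closure.

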### Intervention

The interventions will be performed by licensed acupuncturists with more than 3 years of experience in clinics. According to the traditional acupuncture theory and previous RCTs, the acupuncture study interventions were developed by a consensus of acupuncture experts. Before initiation of the study, the acupuncturists will obtain special training to gain total understanding of the treatment and receive a brochure that shows the acupuncture manipulation with detailed information. Subjects who are assigned to the acupuncture group will receive MMT and JTN treatment for 30 min per session. Meanwhile, those who are randomized to the routine group will receive MMT only. All 18 sessions of JTN treatment will be delivered over 6 weeks (3 per week) and followed by a 4-week follow-up period. The study schedule is shown in Fig. 2.

**Fig. 2 Fig2:**
[figure not shown]
Schedule of enrolment, interventions and assessments

#### Acupuncture group

Base on the theory of JTN, every acupoint group has a special name and contains three or four points. In this study, we will choose three acupoints groups, which will be named *Dingshen-zhen*, *Sishen-zhen* and *Shouzhi-zhen*.

*Dingshen-zhen* will consist of three special points named *Dingshen-I*, *Dingshen-II and Dingshen-III. Dingshen-I* is directly 0.5 *cun* superior to EX-HN3, *Dingshen-II* is directly 0.5 *cun* superior to left GB14 and *Dingshen-III* is directly 0.5 *cun* superior to right GB14. *Sishen-zhen* will consist of two acupoints and two special points named *Sishen-I*, *Sishen-II*, *Sishen-III* and *Sishen-IV*. *Sishen-I* is GV19 and *Sishen-II* are GV21; *Sishen-III* and *Sishen-IV* are, respectively, 1.5 *cun* left and right lateral to the anterior median line and at the same level as GV20. *Shouzhi-zhen* will consist of PC6, PC8 and HT7. The acupuncture points are described in Table 1 and Fig. 3.

**Table 1 Tab1:** Framework of the acupuncture point prescription

Acupuncture points	Description
GV21: Qianding (*Sishen-I*)	On the head, 3.5 B-cun superior to the anterior hairline, on the anterior median line.
GV19: Houding (*Sishen-II*)	On the head, 5.5 B-cun superior to the posterior hairline, on the posterior median line.
GV20: Baihui	On the head, 5B-cun superior to the anterior hairline, on the anterior median line.
*Sishen-III*	On the head, 1.5*cun* left lateral to the anterior median line and at the same level as GV20.
*Sishen-IV*	On the head, 1.5*cun* right lateral to the anterior median line and at the same level as GV20
EX-HN3:Yintang	On the head, between the right medial end of the eyebrow and the left one.
*Dingshen-I*	On the head, directly 0.5*cun* superior to EX-HN3
GB14: Yangbai	On the head, 1B-cun superior to the eyebrow, directly superior to the centre of the pupil.
*Dingshen-II*	On the head, directly 0.5*cun* superior to left GB14
*Dingshen-III*	On the head, directly 0.5*cun* superior to right GB14
HT7: Shenmen	On the anteromedial aspect of the wrist, radial to the flexor carpi ulnaris tendon, on the palmar wrist crease.
PC6: Neiguan	On the anterior aspect of the forearm, between the tendons of the palmaris longus and the flexor carpi radialis, 2B-cun proximal to the palmar wrist crease.
PC8: Laogong	On the palm of the hand, in the depression between the second and third metacarpal bones, proximal to the metacarpophalangeal joints.

Note: The prescribed acupoints come from the WHO Standard Acupuncture Point Locations in the Western Pacific Region

